### OAA Experimental Intervention

All study intervention components were available remotely using a study-specific access code on Belong – Beating Cancer Together [41], a supportive digital platform with a closed community for patients, caregivers, and health care providers at the institution to create networks and connect with other patients [42]. Participants could access the platform on their smartphone or tablet and enter an access code for the study as a closed community in the platform. As opposed to a “one-size-fits-all” approach, the study intervention accords the choice to select the support received. Participants in the experimental group were provided access to all intervention components and chose which specific components to use at any time during study participation. The intervention was developed through rigorous multistakeholder consultation processes, beginning with a comprehensive review of existing OAA-related interventions and evidence by the senior author. Noting no published OAA-specific supportive interventions at the time, the senior author ([name]) secured funding from the Rossy Cancer Network to design and test an OAA intervention, including videos and e-handouts addressing potential side effects and complications related to OAA intake. After meeting with Precare, a company providing educational video resources to patients [43], the first and senior authors gathered initial intervention feedback from oncology nurses, oncologists, researchers, cancer community organizations, patient partners, and informal caregivers or family member representatives. More specifically, these stakeholders provided insights into the content, duration, and overall aspects of the videos and e-handouts, contributing to the refinement of the intervention format and delivery. The final version was thoroughly reviewed by the first and senior author and subsequently integrated into an app [41]. The multimodal OOA intervention components are mentioned in Textbox 1 and Figures 2-4 below.

Multimodal oral anticancer agent intervention components.1. Oral anticancer agent informational videosTopics: General information, side effects, support, fertility and work, and symptoms2. Symptom management tip sheets and additional web-based resourcesTopics: Pain, fatigue, drowsiness, nausea and vomiting, lack of appetite, shortness of breath, depression, anxiety, well-being, insomnia, fear of cancer recurrence, and work3. Call with a nurse navigator.Support and dispatch4. Medication remindersReminder notification pop-ups5. Any combination of services above

**Figure 2 figure2:**
[figure not shown]
The multimodal OAA intervention contained OAA informational videos on general information (seen here), side effects, support, fertility and work, and symptoms. OAA: oral anticancer agent.

**Figure 3 figure3:**
[figure not shown]
The multimodal OAA intervention contained symptom management tip sheets and additional web-based resources on pain, fatigue (seen here), drowsiness, nausea and vomiting, lack of appetite, shortness of breath, depression, anxiety, well-being, insomnia, fear of cancer recurrence, and work. OAA: oral anticancer agent.

**Figure 4 figure4:**
[figure not shown]
The multimodal OAA intervention contained medication reminders as reminder notification pop-ups. OAA: oral anticancer agent.

#### OAA Informational Video

In the context of this study, an evidence-based animated video was developed (Figure 2). The content of the video has been reviewed by multiple stakeholders, including health care providers, patients, and caregivers. The video is available to be watched in English or French, with subtitles available in 16 languages. The video contains 4 parts: general information on oral chemotherapy, side effects, support, fertility and work, and symptoms.

#### Symptom Management Tip Sheets and Additional Web-Based Resources Common Physical and Psychosocial Concerns of Oral Anticancer Therapy

These e-handouts provide knowledge, facts, tips, and additional or telephone resources (Figure 3). The content has been reviewed by multiple stakeholders, including health care providers, patients, and caregivers. The e-handouts are available in French and English on the following 12 topics: pain, fatigue, drowsiness, nausea, lack of appetite, shortness of breath, depression, anxiety, sleep, fear of cancer recurrence, and work. The e-handouts are available for download in PDF format.

#### Follow-up Calls From Oncology Nurse

Participants in the experimental group can receive a call from the oncology nurse specific to their tumor site. A participant may request a phone call at each follow-up e-questionnaire by selecting “I would like to receive a phone call from a nurse” and identifying the topic they would like to discuss. The study coordinator forwards the participant’s name and contact number to the nurse. The participant’s symptom scores from the e-questionnaire are shared with their nurse at this time. The nurse calls the participants and speaks to them on the topic of their choice, and the interaction is documented in the patient chart as a virtual encounter.

#### Medication Reminders

Participants can receive daily e-reminder notifications on their smartphones to take their OAA medication (Figure 4). The e-reminders use preconfigured templates tailored to a 21-day cycle (14 days on per 7 days off) or a 28-day cycle (21 days on and 7 days off) that users must select, with options for once or twice daily reminders. Upon the conclusion of each cycle, users receive a notification prompting them to refill their prescription and reload the 21-day or 28-day cycle template.

In sum, the study intervention was designed to increase SE for OAA adherence through direct mastery experiences (self-management and reminders), vicarious experiences (video), verbal persuasion (phone calls), and feedback (self-management and reminders).

Participants in the control group continued to receive care as usual. This includes follow-up care with their oncologist, contact with their pharmacist and nurse as needed, as well as access to any internal and external supportive services from other health care professionals (eg, psychosocial oncology, social services, physiotherapist, occupational therapist, etc).

### Recruitment, Consent, and Randomization

Participant recruitment occurred at the cancer center in two ways. First, a member of the oncology clinical care team (oncologist, radiation oncologist, nurse, or administrative staff) briefly explained the study and asked patients if they were interested in hearing more about the study. If yes, a member of the study team was informed (in-person, email, or telephone) and contacted the patient. Second, a study poster placed at relevant locations within the cancer center contained the contact information (QR code, email, and telephone number) of the study team. The patients then contacted the team directly.

Interested individuals met with a member of the research team in person or communicated over email or telephone. Study details were provided, and eligibility was verified. If still interested and eligible, a secure link to an electronic consent form was emailed, followed immediately by the baseline questionnaire. Participants were randomly assigned to intervention plus usual care (experimental group, n=26) or usual care only (control group, n=26). Once initial consent was given, those in the experimental group reconsented. Participants in the control group were blinded to group assignment (Article 3.7A of Tri-Council Policy Statement 2) [44]. The randomization sequence was determined on R (R Core Team), a software program, using the randomized R package for clinical trials [45]. Diagram of study design, measurement points, and timeline is shown in Figure 5.

**Figure 5 figure5:**
[figure not shown]
Diagram of study design, measurement points, and timeline.

### Data Collection

In both groups, follow-up e-questionnaires were completed every week for the first month and 2 weeks for the following 4 months, or until treatment was completed (if less than 5 months). Given the considerable variability in the duration of time patients may remain on OAAs, the study duration of 5 months was established as a long enough period in consultation with medical oncologists and pharmacists and was deemed appropriate for assessing the primary outcomes of feasibility and acceptability. Participants were monitored more closely during the first treatment cycle, as this period is critical for identifying potential toxicities and making necessary dosage adjustments. Furthermore, it is crucial to establish positive medication adherence behaviors early in the treatment process [46]. After 5 months or until OAA treatment was completed (if less than 5 months), participants completed the exit questionnaire, and a subset of participants in the experimental group (n=10) and control group (n=10) who had completed the study were invited to participate in a semistructured interview.

All e-questionnaires were completed on Qualtrics, a secure web-based electronic data capture system licensed through McGill University [47]. A data management plan between the university and the affiliated hospital was established for the study (Multimedia Appendix 1). Details of each measure and timepoint are provided in Table 1.

Baseline questionnaires completed by all participants included sociodemographic and medical characteristics, cancer information-seeking preferences, and OAA knowledge.

**Table 1 table1:** Study data collection.

Objective and measure			Instrument		Items, n		Time of collection				
						Baseline		Weekly for the first cycle	Every 2 weeks for cycles 2-5	Final questionnaire	Study completion
**Baseline information**											
	Sociodemographics	—^a^		12		✓		—	—	—	—
	Medical characteristics	—		7		✓		—	—	—	—
	Oral anticancer agent knowledge	—		9		✓		—	—	✓	—
	Cancer information-seeking preferences	Cancer information-seeking profiles		1		✓		—	—	✓	—
**Feasibility of study**											
	Recruitment rate	—		—		—		—	—	—	✓
	Retention rate	—		—		—		—	—	—	✓
	Response to questionnaire	—		—		—		—	—	—	✓
	Intervention uptake	—		—		—		—	—	—	✓
**Prospective acceptability of intervention**											
	Intervention burden perceived effectiveness	Acceptability E-scale for web-based patient-reported outcomes in cancer care		3		✓		—	—	—	—
**Retrospective acceptability of intervention**											
	Intervention burden, perceived effectiveness, and intervention coherence	Acceptability E-scale for web-based patient-reported outcomes in cancer care		5		—		—	—	✓	—
	Exit interview	—		—		—		—	—	—	✓
**Preliminary effects of the intervention**											
	Medication adherence	Proportion of days covered		Chart review		—		—	—	—	✓
	Medication adherence	Medication Adherence Rating Scale ([name])		5		—		✓	✓	—	—
	Medication adherence self-efficacy	Medication Adherence Self-Efficacy Scale		20		✓		✓	✓	—	—
	Symptom distress	Edmonton Assessment Scale revised		12		✓		✓	✓	—	—

^a^Not applicable.

### Measures

#### Sociodemographics and Medical Characteristics

At baseline, participants completed a sociodemographic questionnaire identifying their sex, gender, age, marital status, work status, country of birth, languages spoken, education, and income. They were also asked to complete a medical questionnaire identifying their current diagnosis, cancer stage, coverage of their OAA medication, other medications they are taking on a regular basis, and treatment or treatments received.

#### Cancer Information-Seeking Preferences Scale

This brief, self-report questionnaire based on Self-Evaluation Theory [48] contains 5 statements related to distinct preferences for cancer information. Respondents select the one that best describes how they go about getting information about their cancer: (1) intense—“I seek as much information as possible about my cancer,” (2) complementary—“I seek information about my cancer that adds to what I was told,” (3) peer-focused—“I seek cancer information from others diagnosed with same cancer,” (4) minimal—“I do not seek information about my cancer,” and (5) guarded—“Cancer is stressful enough; I only seek information about my cancer that is hopeful.”

In a large sample (N=2142), participants treated for cancer within the past 6 months responded to the Cancer Information-Seeking Preferences (CISP) scale and patient satisfaction survey (Ambulatory Oncology Patient Satisfaction Survey). A total of 50.2% (1076/2142) selected complementary, 25.2% (539/2142) selected minimal, 14.4% (309/2142) selected guarded, 6.4% (137/2142) selected peer-focused, and 3.8% (81/2142) selected intense, with intense seekers reporting lower satisfaction with cancer care [48,49]. The CISP provides context to the participants’ preferences and uptake of the intervention.

#### Knowledge

The 7-item oral chemotherapy knowledge questionnaire was developed by SA and [name] for the purpose of this study. The scale contains 7 true or false items pertaining to OAA knowledge and self-management (eg, “If I forget to take my oral chemo, I should not double the next dose”).

The study feasibility (aim 1) will be determined by the recruitment rate, retention rate, response rate to e-questionnaires, and uptake of the intervention (Textbox 2).

To assess the acceptability of the intervention (aim 2), intervention burden, intervention coherence, and perceived effectiveness were assessed prospectively at baseline and retrospectively at exit [35] by participants in the experimental group. They were asked to complete the Acceptability E-scale for web-based, patient-reported outcomes in cancer care by Tariman et al [56], requiring a mean score of 80% or higher as the objective. It evaluates the acceptability and usability of computerized health-related programs in oncology. The scale has a reliability of 0.757. It contains 6 items that are rated from 1 (very difficult) to 5 (easy to understand), with total scores ranging from 6 to 30. Table 2 presents constructs and definitions of acceptability as well as baseline and exit questions. In addition, postintervention acceptability was assessed in exit interviews with a subsample of participants (n=20, 10 per group) using an author-generated semistructured interview guide developed based on relevant questions using questions based on the RE-AIM (Reach, Efficacy, Adoption, Implementation, and Maintenance) framework by Glasgow et al [57] to evaluate health behavior interventions (Multimedia Appendix 2). Questions explored participants’ perceptions of OAA information and support, such as “What are your general impressions of the information and support you received during your OAA treatment?” Participant selection for interviews was convenient. Participants were approached in person or over the telephone, and interviews took place in person or over the telephone by the first author, lasting between 30-60 minutes. Only the researchers and participants were present for the interview. After the total number of subsample participants (n=20) had been interviewed, the first author analyzed the interviews to ensure data saturation had been reached. No additional interviews were required.

The potential effects of the intervention (aim 3) will be assessed by comparing experimental and control groups over time, from baseline, every 2 weeks (depending on the outcome), and after the intervention in terms of the following outcomes: medication adherence SE, medication adherence (self-report and pharmacy records), and symptom distress.

Study feasibility objectives.

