**Figure 1 figure1:**
[figure not shown]
Study aims, objectives, and measures.

The second aim is to determine the acceptability of the intervention. The definition and measures of acceptability are based upon theoretical framework of acceptability of health care interventions by Sekhon et al [35], which defines acceptability as a multifaceted construct reflecting the appropriateness of the intervention. A key feature of this framework is the distinction between prospective, concurrent, and retrospective acceptability, emphasizing that acceptability can be assessed before, during, and after the intervention as all 3 can have an impact on participant use and access to the intervention. Although Sekhon et al [35] propose 7 concepts of intervention acceptability, only the 3 most relevant are included herein, namely intervention burden, coherence, and perceived effectiveness.

The third aim of the study focuses on documenting the potential effects of the intervention: As stated in the CONSORT (Consolidated Standards of Reporting Trials) on randomized pilot and feasibility trials [36], pilot trials may assess potential effectiveness using surrogate outcomes—substitute measures used as alternatives to clinical outcomes that may be challenging to assess directly [36]. Herein, potential intervention effects are assessed by comparing experimental and control groups over time, from baseline, every 2 weeks (depending on the outcome), and after the intervention. It is hypothesized that over time, compared to the control group, the experimental group will report higher medication adherence SE, higher medication adherence, and lower overall symptom distress.

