#### Sample Size

Sample size calculation was undertaken using procedures provided by the software program G*Power 3 [37]. As per our statistical consultant, the calculation was undertaken to determine adequate power in the determination of the potential effects of the intervention (aim 3), in which a repeated-measures ANOVA with a within-between interaction would be the statistical test used. The parameters for the power calculation included an effect size of 0.25 (standard medium effect size for ANOVA) [38], α of .01, and a power of 0.95. The sample size was further increased to account for a 30% attrition rate over the study duration, determined to be appropriate given a review of attrition rates in supportive oncology trials found a mean of 26% (95% CI 23%-28%) across 18 trials (ie, the original sample size was 36, total with added 30%, attrition is 52) [39].

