### Data Analysis

Statistical analyses to be performed rely on Microsoft Excel, SPSS (version 25; IBM Corp) [65], and R (R Project for Statistical Computing) software [66]. For PDC, independent sample 1-tailed *t* tests will be performed to calculate the difference between 2 independent means of the experimental and control groups at one time point—study completion. Changes over time in MARS-5, MASES, and ESAS-r will be assessed using repeated-measures ANOVA. Between-group analyses will be conducted to examine how each group changed over time, and within-group analyses will be conducted to examine how participants changed over time.

The relationship between objective (PDC) and subjective (MARS-5) measures of medication adherence will be assessed using Spearman correlation coefficients. Oral chemotherapy knowledge at baseline and study exit will be compared using paired sample 1-tailed *t* tests.

Interviews were conducted individually, audio recorded, and transcribed verbatim by the first author, a doctoral candidate at the time with experience in qualitative research in oncology working on her dissertation. A reflexive journal was kept to document thoughts and feelings to recognize, acknowledge, and mitigate the influence of her role as a researcher and as someone with lived experience as an informal caretaker for a parent. Interview data were analyzed by the same author using thematic analysis as described by Braun and Clarke [67,68], beginning with several thorough readings of participant verbatim content to familiarize the researcher with the data and the identification of significant statements relating to the phenomenon under investigation [69]. Next, significant statements were placed into initial categories and organized into broader themes and subthemes. Themes and subthemes were reviewed, redefined, renamed, and explored as needed until no new themes emerged from the data.

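### MARS-5 has no baseline, so the stated change-over-time test cannot detect a self-reported adherence benefit that is present from the first follow-up and then held

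*Protocol article*

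**What the plan says.** Purpose of Study states that potential effects are assessed by comparing the arms "from baseline, every 2 weeks (depending on the outcome), and after the intervention". The aim 3 paragraph under Measures repeats this: "comparing experimental and control groups over time, from baseline, every 2 weeks (depending on the outcome), and after the intervention". It lists medication adherence self-efficacy, medication adherence by self-report and by pharmacy records, and symptom distress.

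Table 1 gives the collection times for these outcomes:

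| Measure | Baseline | Weekly, first cycle | Every 2 weeks | Final questionnaire | Study completion |
|---|---|---|---|---|---|
| MARS-5 | no | yes | yes | no | no |
| MASES | yes | yes | yes | no | no |
| ESAS-r | yes | yes | yes | no | no |
| PDC (chart review) | no | no | no | no | yes |

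Sample Size says that for aim 3 "a repeated-measures ANOVA with a within-between interaction would be the statistical test used", with an "effect size of 0.25 (standard medium effect size for ANOVA) [38], α of .01, and a power of 0.95". Data Analysis says "Changes over time in MARS-5, MASES, and ESAS-r will be assessed using repeated-measures ANOVA", and describes the between-group analyses as looking at how each group changed. PDC is compared between arms by a one-tailed t test at study completion.

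**The concern.** A comparison from baseline cannot be made for MARS-5, because its first value is taken after randomisation, when the experimental arm already has access to the intervention. With only post-randomisation values, a group-by-time test measures whether the gap between arms widens or narrows during follow-up. It does not measure whether there is a gap.

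A gap that opens early and stays open is a pattern the article gives reason to expect. Data Collection stresses that good adherence behaviour should be established early in treatment. If that happens, the named test would return a null result on self-reported adherence even though the arms differ throughout. Turning to a different term after seeing the data would then be a post hoc choice.

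**Working it through.** **The plan's own figure.** The article gives f = 0.25, alpha 0.01 and power 0.95, but not the number of measurements m or the correlation ρ. For the within-between interaction with two groups, λ = f²·N·m/(1 − ρ), df1 = m − 1 and df2 = (N − 2)(m − 1). Taking m = 6 and ρ = 0.5 (assumed), λ = 0.0625 × 36 × 6/0.5 = 27 on 5 and 170 df, and power is 0.951. So N = 36 is reproduced; other pairs such as m = 3 with ρ = 0.7 also give it. Attrition: 36/0.70 = 51.4, rounded up to 52. The planned size is therefore consistent with the interaction being the intended test.

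**What the interaction sees in MARS-5.** Let the arm difference be δ at each of m follow-ups, with no baseline. The interaction depends on the difference at each time minus the average difference: δ − δ = 0 at every time. Hence λ = 0 and the rejection rate equals alpha for any δ, ρ or m. Simulations agree: 4.2% at 0.05 and 0.9% at 0.01 (3,000 runs, δ = 0.5 SD); 0.96% at 0.01 (20,000 runs, δ = 0.8 SD).

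**What the average over follow-up sees.** Inputs:
- Final sample of 23 and 18 (Results).
- δ = 0.5 SD, compound symmetry and ρ from 0.3 to 0.7: assumed.
- m = 12 from the schedule in Data Collection (4 weekly, then 8 two-weekly), or m = 11 if the maximum of CAD 120 at CAD 10 per set covers baseline plus 11.

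The variance of a participant's mean is v = [1 + (m − 1)ρ]/m in SD² units, and λ = δ²·[n1·n2/(n1 + n2)]/v on 1 and 39 df. Here n1·n2/(n1 + n2) = 23 × 18/41 = 10.098. For m = 12 and ρ = 0.5, v = 6.5/12 = 0.5417 and λ = 0.25 × 10.098/0.5417 = 4.66.

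| Follow-ups | ρ | v | λ | Power at 0.05 | Power at 0.01 |
|---|---|---|---|---|---|
| 12 | 0.3 | 0.358 | 7.05 | 0.735 | 0.486 |
| 12 | 0.5 | 0.542 | 4.66 | 0.558 | 0.306 |
| 12 | 0.7 | 0.725 | 3.48 | 0.444 | 0.215 |
| 11 | 0.3 | 0.364 | 6.94 | 0.729 | 0.479 |
| 11 | 0.5 | 0.545 | 4.63 | 0.555 | 0.303 |
| 11 | 0.7 | 0.727 | 3.47 | 0.443 | 0.214 |

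**Would a MARS-5 baseline have solved it?** Only in part. Add one baseline point with no difference: λ = δ²·10.098·[m/(m + 1)]/(1 − ρ). For m = 12 and ρ = 0.5 this is 0.25 × 10.098 × (12/13)/0.5 = 4.66. That happens to equal the λ above, but it is now spread over 12 df instead of 1. Power is 0.224 at 0.05 and 0.081 at 0.01, against 0.558 and 0.306 for the average.

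**The case against.** The strongest reply is that the article does not rule out the right analysis. A two-arm repeated-measures ANOVA also yields a group main effect, Data Analysis plans between-group analyses, and the hypothesis in Purpose of Study is a level difference: higher adherence in the experimental arm over time. The interaction is named only in the sample-size paragraph, and the exact contrast might be left to an analysis plan that is not shown. This stands in part. The main effect is available, but the article does name a test for aim 3, and it words even the between-group analysis as change. It therefore points to the term that cannot answer the hypothesis for MARS-5.

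Other points on that side are correct and limit the concern:
- PDC is the second adherence measure. It is compared at one time point, needs no baseline and can show a steady benefit.
- MASES and ESAS-r have baselines.
- A missing MARS-5 baseline is defensible. Sample and Inclusion Criteria allow enrolment before the first dose, when there is no adherence to this treatment to report.
- The schedule sentence covers several outcomes and carries a qualifier, so the mismatch with Table 1 is mild. On its plain reading, though, the qualifier attaches to the two-weekly interval and not to the baseline.

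A reader might infer that the trial would miss any steady adherence benefit, or report none. The documents do not support that, given PDC and the available main effect. A reader might also infer, from the empty final-questionnaire column, that none of the three scales has an end-of-intervention value and that this adds to the problem. It does not: two-weekly forms run to month 5 or the end of treatment, so the last one falls at about the same point as the exit questionnaire. The empty column leaves only loose wording.

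**Conclusion.** The concern holds for MARS-5 and for the change-over-time term only. For a benefit present from the first follow-up and then constant, that term rejects at alpha; this follows from the design and rests on no assumed effect size. If the benefit instead grew or faded during follow-up, the term would have some power.

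The size of what is lost does rest on assumptions. With 23 v 18, 0.5 SD and 12 follow-ups, the averaged arm difference has about 56% power at 0.05 and 31% at 0.01 at correlation 0.5. For correlations from 0.7 to 0.3 the range is 44% to 74% at 0.05 and 22% to 49% at 0.01; with 11 follow-ups it is almost the same. The effect size, the correlation and its compound-symmetry form are not in the article.

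Severity is minor. Feasibility and acceptability are the primary outcomes, and aim 3 explores potential effects in a pilot.

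**What to change.** In the aim 3 paragraph under Measures and in Data Analysis, state that the MARS-5 comparison is the arm difference averaged over all follow-up assessments: the group main effect, or the equivalent one-degree-of-freedom contrast in a mixed model. Restrict the comparison from baseline to MASES and ESAS-r, there and in Purpose of Study. No MARS-5 baseline is needed.

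As a separate wording point, say that the measurement after the intervention is the last scheduled two-weekly assessment (month 5 or end of treatment), since Table 1 does not put the three scales in the final questionnaire.

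The cost is a few sentences. The data are already collected, and the article says that results are still to be published separately, so the contrast should be stated in or before that report, with the date on which it was fixed.
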